**Methods:**

A total of 172 community-dwelling adults aged 65 years or older with an anxiety and/or depressive disorder will be randomly allocated to either an enhanced CBT plus social participation program (n = 86) or standard CBT (n = 86). Both treatments will be delivered during 12 weekly individual sessions utilising structured manuals and workbooks. Participants will be assessed at pre-treatment, post-treatment, and 12-month follow-up. The primary outcome evaluates mean change in clinician-rated diagnostic severity of anxiety and depressive disorders from baseline to post-treatment (primary endpoint) based on a semi-structured diagnostic interview. Secondary outcomes evaluate changes in symptomatology on self-report anxiety and depression measures, as well as changes in social/community participation, social network, and perceived social support, loneliness, quality of life, and use of health services. Economic benefits will be evaluated using a cost-utility analysis to derive the incremental cost utility ratios for the enhanced CBT program.

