The primary outcome is the mean changes in Clinical Severity Rating (CSR) across all anxiety and depressive disorders on the ADIS-5 [24] at post-treatment. The ADIS -5 is a semi-structured interview for diagnosing psychiatric conditions according to DSM -5 [23] criteria. The CSR provides an overall severity rating comprising the level of distress and impairment associated with each DSM disorder from 0 (none) to 8 (very severe). A CSR of 4 or higher indicates that the disorder meets or exceeds the threshold for a formal DSM-5 diagnosis. The mean severity rating is calculated to examine overall changes in diagnostic severity over time. This interview will be administered by blinded clinical psychologists, psychologists, or provisional psychologists who will be trained in the interview administration and receive regular supervision to assist with diagnostic decisions.

Secondary outcomes will be measured by:

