1) Mean changes in CSR across all anxiety and depressive disorders based on the ADIS-5 at 12-month follow-up.2) Changes in symptomatology at post-treatment and 12-month follow-up on the following measures:**Geriatric Anxiety Inventory** [GAI; 28]. The GAI is a 20-item self-report measure of anxiety in older adults.**Geriatric Depression Scale** [GDS; 29]. The GDS is a 30-item self-report measure of depression for use in older adult populations.**Depressive Symptoms Inventory–Suicide Subscale** [30] is a 4-item measure of suicidal ideation.2) Changes in social participation/connection at post-treatment and 12-month follow-up on the following measures:**De Jong Gierveld Loneliness Scales** [31], which measures feelings of loneliness andperceived social isolation with 11 items.**Lubben Social Network Scale** [LSNS; 32]. The LSNS is a commonly used tool to assess social connections in older adult populations. The 18-item scale assesses the frequency and quality of family, friendship and neighbour support.**The Australian Community Participation Questionnaire-Short Form [33]** The 12-item short form of the ACPQ measures frequency of participation in seven different social activities (contact with extended family, friends and neighbours, contact with friends and family, attending organised community events, volunteering and political protest).3) Cost utility of the interventions on the following measures:**Assessment of Quality of Life** [AQoL-8D; 35, 37]. The AQoL-8D measures quality of life and health outcomes across eight domains (independent living, relationships, mental health, coping, pain, senses, self-worth, and happiness).**Use of Care Services.** The Use of Service survey is developed by the research team to assess use of health and community care services in the preceding six months, including hospital services, medical services, allied health services, community-based services, and diagnostic services, supplemented with linked data from the NSW Centre for Health Record Linkage (CHeReL) on Admitted Patient data, Emergency Department data, and Mental Health Ambulatory data, along with Medicare Benefit Schedule (MBS) and Pharmaceutical Benefit Schedule (PBS) data.**iMTA Productivity Cost Questionnaire** [iPCQ; 36]. The iPCQ is a standardised instrument to measure and value health-related productivity losses including presenteeism and absenteeism in paid and unpaid work.

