### 2.12 Statistical methods

Data will be analysed using intention-to-treat principles. All participants will be included in analyses based on the condition to which they were initially allocated. Multiple imputation will be used to manage missing data. The efficacy of the programs will be established using mixed model analysis to compare the mean differences in clinical diagnostic severity (established by clinicians who are blind to treatment allocation) and scores on self-report measures at pre-treatment, post-treatment, and at a 12-month follow-up period.

Analysis will be a mixed model with random subject effect, fixed effects relating to group allocation (between-group), time (within-subject) and covariates. Interaction contrasts will be used if the time x group interaction reaches statistical significance, but the main effect contrast will be used if not.

Statistical inference will be based on the nonparametric bootstrap if the assumption of Normality is violated. The same process will be used for the secondary hypotheses to compare the groups on all outcome measures. Differences between groups in baseline characteristics, and therapy factors (e.g., sessions attended, therapist alliance) will be examined and controlled for in analyses.

In addition, an economic evaluation will be undertaken to measure the relative benefit in health outcomes and resource use for the enhanced intervention compared to standard CBT. Moderation analyses will examine the impact of moderators on treatment outcomes.

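### The primary test switches from the change contrast to a group main effect when the interaction is not significant, so the data choose the estimand and the 5% level is not kept

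*Protocol article*

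**What the plan says.** Section 2.6 of the protocol article defines the endpoint: "The primary outcome is the mean changes in Clinical Severity Rating (CSR) across all anxiety and depressive disorders on the ADIS-5 [24] at post-treatment". The abstract agrees and labels the baseline-to-post-treatment change as the primary endpoint. Section 2.6 lists the 12-month result among the secondary outcomes: "Mean changes in CSR across all anxiety and depressive disorders based on the ADIS-5 at 12-month follow-up". It also places the baseline assessment (T1) before randomisation.

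Section 2.12 specifies a "mixed model with random subject effect, fixed effects relating to group allocation (between-group), time (within-subject) and covariates". It is applied to clinician-rated severity and to "scores on self-report measures at pre-treatment, post-treatment, and at a 12-month follow-up period", so baseline is one of the modelled visits. The contrast is then selected as follows: "Interaction contrasts will be used if the time x group interaction reaches statistical significance, but the main effect contrast will be used if not". The same procedure is extended to the secondary hypotheses, for comparing the groups on every outcome measure.

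Section 2.7 sizes the trial for a single comparison: Cohen's d of 0.5, 90% power, two-sided alpha of 0.05, 172 participants. Nothing in the article exempts the primary endpoint from the selection rule or adjusts alpha for it.

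**The concern.** The two branches estimate different quantities. The interaction branch estimates a difference in change. The fallback estimates the difference between arms averaged over T1, post-treatment (T2) and 12 months (T3). Only the first can be the declared endpoint, and a significance test on the trial's own data decides which one is reported.

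Three consequences follow:

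- **Error rate.** There are two routes to a positive finding and no adjustment for having both.
- **Dilution and imbalance.** The fallback includes a visit at which treatment cannot have acted. This shrinks a real effect, and any chance baseline imbalance enters the estimate as if it were treatment benefit.
- **A secondary visit steers the primary test.** With three visits the interaction has 2 degrees of freedom, so the T3 result helps decide how the T2 endpoint is tested.

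At stake are the 5% level of the main efficacy claim and whether the reported number is the one the trial was designed and powered for.

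**Working it through.** **Inputs from the article.** 86 per arm, d = 0.5, two-sided alpha 0.05, 90% power (2.7); three visits, with T1 before randomisation (2.6); random subject effect (2.12). The article gives no correlation between visits, so rho = 0.3, 0.5 and 0.7 are assumed. Effects are in SDs of a score at one visit.

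**The plan's own figure.** n per arm = 2(1.960 + 1.282)² / 0.5² = 84.06, which rounds up to 85. The t-based calculation gives 85.03, which rounds up to 86 per arm, 172 in total. The stated size reproduces and is not in dispute; it is the size for one fixed comparison.

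**Dilution in the fallback** (no correlation needed). Main effect = (difference at T1 + T2 + T3) / 3, with T1 = 0 in expectation:

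- 0.5 SD sustained: (0 + 0.5 + 0.5)/3 = 0.33
- half faded by T3: (0 + 0.5 + 0.25)/3 = 0.25
- fully faded by T3: (0 + 0.5 + 0)/3 = 0.17

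**Error rate under no effect.** When the random-intercept model is correct, the interaction and main-effect tests are practically independent. If a significant interaction alone counts as success, the rate is 1 − 0.95² = 0.0975. If the T2 contrast must also be significant after the interaction test, that route contributes about 0.025 and the fallback 0.95 × 0.05 = 0.0475, together about 0.0725. Simulation of 40,000 null trials, 86 per arm, complete data:

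| Rule | rho 0.3 | rho 0.5 | rho 0.7 |
|---|---|---|---|
| Interaction then T2 contrast, else main effect | 0.071 | 0.070 | 0.071 |
| Significant interaction, else main effect | 0.096 | 0.095 | 0.098 |
| Fixed T2 contrast | 0.050 | 0.050 | 0.050 |

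If either the T2 or the T3 contrast may count after a significant interaction, the rate is 0.087 to 0.089.

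**Baseline imbalance.** In null trials where the fallback was significant, the mean baseline difference in the direction of the apparent effect was 0.26 to 0.31 SD. It existed before treatment.

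**Use and power of the fallback with a real effect** (10,000 trials per scenario):

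| True effect at T2, T3 | | rho 0.3 | rho 0.5 | rho 0.7 |
|---|---|---|---|---|
| 0.5, 0.5 | interaction not significant | 17.7% | 6.8% | 0.6% |
| | power of main-effect test | 0.84 | 0.76 | 0.68 |
| 0.5, 0.25 | interaction not significant | 31.0% | 15.6% | 2.9% |
| | power of main-effect test | 0.61 | 0.51 | 0.44 |

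**Influence of T3.** With no effect at T2 and 0.5 SD at T3 only, the rule that requires the T2 contrast or the main effect declares success in 10.8%, 6.8% and 5.1% of trials (rho 0.3, 0.5, 0.7). The fixed T2 contrast stays at about 5%.

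**The case against.** **The article does not say which main effect it means.** Group and time are both fixed effects. If the fallback were the time effect (both programmes improved), there would be no second route to a superiority claim, and the T2 claim would be conservative at about 2.5%. However, section 2.12 extends the same procedure to comparing the groups on all outcomes, and a time effect compares no arms. The group effect is the reading that fits a superiority trial.

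**Some error figures mix in another problem.** With equal SDs and unequal correlations (0.3, 0.25, 0.6), the rule rejects in 8.2% of null trials, or 9.8% if any interaction contrast may count. A random-intercept model does not fit that pattern, and the fixed T2 contrast itself then rejects in about 6.5%. This stands. The inflation due to the switching rule alone is about 2 percentage points for the T2 endpoint. The 9% to 10% figures apply only if a T3 contrast or the omnibus interaction counts as success.

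**Baseline may be handled as a covariate.** Section 2.12 mentions covariates and control of baseline differences. With baseline CSR as a covariate and only T2 and T3 as responses, the dilution by baseline would disappear. The article does not say this and lists pre-treatment among the visits compared. Even then the fallback would average T2 with T3, which is not the primary endpoint.

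**The fallback may rarely be used.** With a real effect and high correlation this is right (0.6% to 2.9% at rho 0.7). Under no effect, where the error rate is defined, it is used in about 95% of trials.

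**An analysis plan may settle it.** The article states the rule outright, so it is not a detail left open, and a plan that follows it inherits the fault.

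**Conclusion.** The rule is wrong as written. It lets a preliminary test choose between the declared endpoint and a different quantity, and it does not keep the two-sided 5% level. With a correctly fitting random-intercept model, complete data and 86 per arm, the error rate is about 7% if the T2 contrast must be significant, and about 9% if either interaction contrast may count. Both hardly vary with rho from 0.3 to 0.7.

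The dilution to 0.33, 0.25 or 0.17 SD is arithmetic; it assumes only that baseline is a modelled response and that the fallback is the group effect. How often the fallback would be reached under a real effect depends on the unknown correlation and is the least certain part.

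**What to change.** Replace the selection sentence in section 2.12 with one primary analysis: the between-group difference in change in mean CSR from baseline to post-treatment, estimated from the mixed model and tested at two-sided 0.05 whatever the omnibus interaction shows. Make the 12-month contrast secondary. Do not use a group main effect that includes the baseline visit as evidence of efficacy. Apply the same to the secondary measures.

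Two details belong with it. First, use a covariance structure that does not force equal correlations across visits, such as an unstructured one; otherwise the fixed contrast may not hold 5% either. Second, consider the baseline-adjusted T2 difference, which targets the same effect with less variance. By the normal approximation, the standard error is √[(2/86) × 2(1 − rho)] for the change contrast and √[(2/86) × (1 − rho²)] for the adjusted difference. For a 0.5 SD effect, power is 0.79, 0.91 and 0.99 for change, and 0.93, 0.97 and above 0.99 when adjusted (rho 0.3, 0.5, 0.7).

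The cost is a sentence or two of text, with no new data and no larger sample. The second route to significance is lost: at rho 0.3 the switching rule rejects in 0.90 of trials with a sustained effect, against 0.79 for the unadjusted change contrast. Part of that gain comes from a test of a different quantity, and baseline adjustment more than recovers the difference.

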### 2.4 Eligibility criteria

Eligible participants are adults aged 65 years or older with a primary diagnosis of an anxiety and/or unipolar depressive disorder according to the Diagnostic and Statistical Manual of Mental Disorders– 5^th^ Edition (DSM-5) [23] criteria assessed by the Anxiety Disorders Interview Schedule for DSM-5 (ADIS-5) [24]. In addition, participants will need to have adequate understanding of the English language as indicated by the ability to read a local newspaper.

Individuals will be excluded if they have current psychotic or bipolar traits, active suicidal intent, significant uncorrected hearing loss and likely moderate to severe dementia as screened by the six-item Cognitive Impairment Screener [25]. Participants currently using psychotropic medications (e.g., anxiolytic and antidepressant medication) will not be excluded, but participants will need to be stabilised on medications for one month before baseline assessment. Participants will report medication type, dosage and frequency of use, and whether the medications were prescribed for management of depression or anxiety. All medication changes will be noted at each assessment and those related to anxiety and mood management will be statistically controlled in analyses.

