### 2.5 Interventions

Both the standard and enhanced CBT programs are guided by structured manuals for therapists and supported by workbooks containing homework exercises and lesson summaries for participants. In both treatment conditions, sessions will be run by clinical psychologists and provisional psychologists trained in delivery of the treatment protocols. To control for therapist differences, all therapists will be trained in and will conduct both treatments (allocated randomly). Supervision will be provided by chief investigators (CIs) and associate investigators (AIs) with treatment adherence and differentiation between conditions as a core focus. All therapy sessions will be recorded, and a random 20% will be rated by an independent expert unaware of the study hypotheses for adherence to the therapeutic manual using a codebook and form based on Waltz, Addis, Koerner, & Jacobson [26]. Therapy alliance will be measured using the 19-item Helping Alliance Questionnaire [HAq-II; 27].

The standard program will comprise our empirically validated CBT program for older age anxiety and depression, *Ageing Wisely*. The *Ageing Wisely* program consists of 12 weekly individual one-hour sessions to teach practical skills to help manage anxiety and depression including: goal setting, activity scheduling, problem solving, graded exposure, cognitive restructuring, and sleep hygiene. Skills such as assertive communication training, as well as examples that illustrate application of CBT skills to increase social connections, were not included in the standard CBT program. Homework activities are assigned to promote skill acquisition and generalisation.

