### 2.6 Outcomes and participant timeline

The study has a longitudinal design conducted over 12 months with three assessment points. Outcome measures will be collected at baseline (T1) (prior to randomisation); post-treatment (T2) (14 weeks from baseline assessment); and 12-month follow-up (T3) (12 months from start of therapy) by blinded assessors. The primary and secondary outcome measures are presented in Table 1. Measures include self-reported measures and measures administered by an independent assessor (independent clinician) blind to treatment allocation at each of the time points. In addition to blinding of treatment type by the research assistant, at the start of each assessment participants will be asked not to confer the details of their treatment, including treatment condition, to the independent assessors. Clinician-report measures (treating clinician) are also administered.

**Table 1 pone.0269981.t001:** Primary and secondary outcome measures by time interval.

Instrument	Domain	Type^a^	Time Interval^b^^a2^			Reference
			T_1_	T_2_	T_3_	
Demographic Inventory	Demographics	SR	✓	✓	✓	
GAI-20	Anxiety	SR	✓	✓	✓	[28]
GDS-30	Depression	SR	✓	✓	✓	[29]
DSI-S	Depression/Suicide	SR	✓	✓	✓	[30]
ADIS-5	Psychopathology	BA	✓	✓	✓	[24]
DJGLS-11	Social Connection	SR	✓	✓	✓	[31]
LSNS	Social Network	SR	✓	✓	✓	[32]
ACPQ-12	Social Participation	SR	✓	✓	✓	[33]
PID-5 -BF	Personality Traits	SR	✓	✓	✓	[34]
HAq-II	Therapeutic Alliance	SR		✓		[27]
AQoL	Health Related Quality of Life	SR	✓	✓	✓	[35]
Use of Care Services Questionnaire	Cost-Effectiveness	SR	✓	✓	✓	N/A
iPCQ	Cost-Effectiveness	SR	✓	✓	✓	[36]

NOTE: GAI-20 = Geriatric Anxiety Inventory– 20 items; GDS-30 = Geriatric Depression Scale– 30 items; DSI-S = Depressive Symptoms Inventory–Suicide Subscale; ADIS-5 = The Anxiety Disorders Interview Schedule 5^th^ edition; DJGLS-11 = De Jong Gierveld Loneliness Scales—11 items; Lubben Social Network Scale; ACPQ-12 = Australian Community Participation Questionnaire– 12 item; PID-5 –BF = The Personality Inventory for DSM– 5; HAq-II = Helping Alliance Questionnaire; AQoL = Assessment of Quality of Life; iPCQ = iMTA Productivity Cost Questionnaire.

^a^SR = Self-eeport scales administered by participants; OS = Observer scale administered by treating clinician; BA = Scale administered by independent blind assessor

^b^T_1_ = Baseline assessment; T_2_ = 14-week post-treatment assessment; T_3_ = 12-month follow-up assessment.

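### Section 2.12 and section 2.4 commit the efficacy analyses to adjusting for variables that arise after randomisation (sessions attended, alliance, medication changes), so the adjusted contrast may no longer be the total effect of assignment

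*Protocol article*

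**What the plan says.** Section 2.12 sets the principle: "Data will be analysed using intention-to-treat principles". It then gives the model: "Analysis will be a mixed model with random subject effect, fixed effects relating to group allocation (between-group), time (within-subject) and covariates". The interaction contrast is used if the time x group interaction is significant, and the main-effect contrast otherwise. The following paragraph, after extending the approach to the secondary hypotheses, ends: "Differences between groups in baseline characteristics, and therapy factors (e.g., sessions attended, therapist alliance) will be examined and controlled for in analyses".

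Section 2.4 makes a parallel commitment on medication: "All medication changes will be noted at each assessment and those related to anxiety and mood management will be statistically controlled in analyses".

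Neither sentence limits the adjustment to secondary, sensitivity or exploratory work. Mediation has its own subsection (2.12.1), which names demographic, personality and social participation factors but not sessions, alliance or medication change. The outcome at stake is stated in section 2.6: "The primary outcome is the mean changes in Clinical Severity Rating (CSR) across all anxiety and depressive disorders on the ADIS-5".

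**The concern.** Randomisation makes the arms comparable on everything that precedes it. It gives no such protection to variables that arise afterwards. If allocation changes one of them, adjusting for it does two things. It subtracts whatever part of the treatment effect runs through that variable. It also opens a path through unmeasured causes shared by the variable and the outcome, such as motivation or worsening mood. Medication change raises a further problem, because it can be a response to the severity that the CSR records.

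The trial asks whether offering enhanced CBT, rather than standard CBT, lowers diagnostic severity. A contrast conditional on alliance, attendance or medication change answers a different question, and a larger sample does not turn it back into the first.

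**Working it through.** **1. When each variable arises.** Section 2.6 gives the clock: "Outcome measures will be collected at baseline (T1) (prior to randomisation); post-treatment (T2) (14 weeks from baseline assessment". The 12-month follow-up comes later still.

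| Variable | Source | Timing |
|---|---|---|
| Sessions attended | 2.12 | Exists only once therapy has begun |
| Alliance | 2.5: "Therapy alliance will be measured using the 19-item Helping Alliance Questionnaire"; Table 1 ticks it once, at T2 | After randomisation |
| Medication changes | 2.4: "participants will need to be stabilised on medications for one month before baseline assessment"; changes noted at each assessment | Those noted at T2 and T3 are post-baseline and, apart from any in the gap between baseline and allocation, post-randomisation |

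**2. The plan's own figure.** For d = 0.5, 90% power and two-sided alpha 0.05, the normal approximation gives 2(1.960 + 1.282)²/0.5² = 84.1, so 85 per arm. The t test needs 85.03, so 86 per arm and 172 in total, with power 90.3%. The stated 172 reproduces and is not in dispute.

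**3. Bias at a single visit.** The documents give no arm effect on these covariates and no link between them and CSR, so the inputs here are assumptions. Let G be the arm, M the covariate and U an unmeasured common cause, with within-arm SDs of 1:

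- M = aG + uU + error
- Y = τG − uU + error

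The within-arm slope of Y on M is −u². The adjusted arm coefficient is therefore τ + a·u². With τ = −0.5, a = 0.3 and u = 0.5, it is −0.5 + 0.3 × 0.25 = −0.425. If M also acts on the outcome with effect b, a further a·b is removed, for example 0.3 × 0.3 = 0.09.

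**4. The planned model.** Take three visits and a random subject effect, no arm effect at T1, τ = −0.5 at T2 and T3, and a common cause that acts on CSR at T2 and T3 but not at T1.

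- *Single-valued covariate, main effect only, interaction contrast.* The contrast compares within-person change between arms. The covariate adds the same amount at every visit and cancels. Simulated: −0.51 with and without it.
- *Same covariate, main-effect contrast.* Unadjusted: (0 − 0.5 − 0.5)/3 = −0.333. The average slope on M is (0 − 0.25 − 0.25)/3 = −0.167. Adjusted: −0.333 + 0.3 × 0.167 = −0.283. Simulated: −0.33 becomes −0.28.
- *Covariate x time terms added, interaction contrast.* The slope at T2 is free, so the contrast is −0.425 by step 3. Simulated: −0.44.
- *Medication change, zero at T1 and non-zero later, interaction contrast.* It enters the change from T1 to T2 directly. Algebra: −0.425. Simulated: −0.43.

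**5. Limits of these figures.**

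- With a = 0 the bias term a·u² is zero. Single-visit simulations with a = 0 returned 0.50 and 0.00 for true effects of 0.50 and 0, with type I error 4.6% to 5.1%.
- The sign depends on the inputs. If the arm raises a covariate that goes with higher CSR, step 3 gives −0.5 − 0.075 = −0.575, an overstatement.
- If the common cause acts equally at all three visits, covariate x time terms add no bias to the interaction contrast, but the main-effect contrast becomes −0.333 + 0.075 = −0.258.

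**The case against.** **Intention-to-treat is kept.** Section 2.12 explains the principle as analysing everyone in the condition to which they were allocated, and adjustment does not alter that. A reader might infer that the plan breaks its own intention-to-treat rule. The text does not support this. The population is preserved, and what changes is the quantity estimated.

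**The model protects one contrast.** This stands for sessions and alliance, if each is one value per participant entered as a plain main effect, and multiple imputation completes the data. A reader might infer that the primary effect is biased in every case. A reader might also regress a single post-treatment score on arm and alliance. With a 0.3 SD arm effect and loadings of 0.5 to 0.6, that turns a true 0.5 into 0.39 to 0.43, with power of 77% to 81% and type I error of about 8% to 11%. Those figures do not describe the planned repeated-measures model. The protection still does not cover the main-effect contrast, covariate x time terms or time-varying medication change.

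**The inputs are assumed.** Both arms have 12 weekly one-hour individual sessions, and all therapists deliver both treatments, so nothing in the text establishes a 0.3 SD shift. This limits what can be said about size. It does not remove the concern. The arms differ in rationale, assertiveness training and social focus, and section 2.12 ties control of therapy factors to differences between groups.

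**The analysis plan may settle it.** A full covariate list is commonly left to that document, and its absence here is no fault. But the two sentences are stated rules, and an analysis plan that followed them would carry the same problem. The sentence in section 2.12 also invites the choice of baseline covariates by observed imbalance. That is a lesser point about how they are chosen, and no complaint that they are not listed.

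**Conclusion.** The plan is wrong as written on this point. It commits the efficacy analyses, without restriction, to controlling for variables that follow randomisation. If the arm affects any of them, the adjusted contrast is not the total effect of assignment in three situations: the fallback main-effect contrast, covariate x time terms, and medication change as a time-varying covariate. The time x group contrast is unaffected by a once-measured covariate entered as a plain main effect in complete data.

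Under the assumptions in the working (arm effect 0.3 SD, common-cause loading 0.5, common cause acting after baseline, effect sustained to 12 months), a true -0.5 SD interaction contrast is reported as about -0.43 to -0.44 in the affected cases, and the main-effect contrast moves from about -0.33 to -0.28. These figures illustrate the mechanism and are not a forecast. The documents fix neither size nor direction, and there is no bias if the arm leaves the covariate unchanged.

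**What to change.** Amend two sentences.

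- **Section 2.12:** remove therapy factors from the covariates of the primary and secondary efficacy models. State that covariates are limited to pre-randomisation variables chosen in advance, whatever imbalance is observed. Which variables to choose is for the trial team. Baseline CSR is already an outcome row in the planned model, so using it as a covariate as well would need a different model.
- **Section 2.4:** keep the recording of medication changes, but replace the commitment to control for them with one to report them by arm. Medication use at baseline remains available as a covariate.

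Sessions attended, alliance and medication changes can then be described by arm and used in analyses labelled as supplementary or mediation, where the different question they answer is stated.

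The cost is wording only. No new data are needed and the sample size of 172 does not change. If an analysis plan already exists, its covariate list should be checked against the same rule.
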